**Methods:**

This is a three-group, parallel, single-blind, randomized controlled trial (RCT). In total, 210 adults (aged 18–75 years) diagnosed with an AUD will be invited to participate in a 12-week intervention. The primary study outcome is alcohol consumption measure by the Timeline Follow-back method and the Alcohol Use Disorders Identification Test (AUDIT). Secondary outcomes include: depression, anxiety, perceived stress, sleep quality, physical activity levels, fitness, self-efficacy, health-related quality of life, and cognition. Blood samples will be taken to objectively assess heavy drinking, and saliva to measure cortisol. Acute effects of exercise on the urge to drink alcohol, mood, and anxiety will also be assessed.

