### Study design, randomization, and blinding

This is a three-group, parallel, single-blind, RCT to compare the effects of three 12-week interventions (yoga, aerobic training, and treatment as usual (TAU)) on alcohol consumption. The proposed flow of participants through the trial is shown in Fig. 2. Assessments will be made at baseline (pre randomization) and post treatment (week 13). The randomization sequence will be computer generated and performed externally by a statistician at the Karolinska Institutet. A researcher not involved in the trial, but located at the clinic where the study will be managed, will then receive the allocation in sequentially numbered, opaque envelopes. In this way, the allocation sequence will be concealed from the person responsible for randomizing study participants. Trained research assistants, including a qualified nurse or psychologist, will administer each assessment in person at Riddargatan 1. The 12-week “treatment” will commence approximately 1 week after the baseline assessment when participants begin training/treatment (baseline physical activity levels will be measured for 1 week before this, see description below). To optimize recruitment and minimize dropouts, those randomized to TAU will be offered the 12-week exercise intervention after they have completed the follow-up assessment. The study endpoint is week 13 (post-treatment). All participants will be aged 18 to 75 years and residents of Stockholm County. Treatment allocation will not be concealed from either participants or the researchers conducting the baseline assessments. However, as a different research assistant will perform the post-treatment assessments, follow-up assessors will be blind to group allocation. Unblinding will only occur in the event that a participant chooses to withdraw from the study.

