#### Baseline and follow-up assessments

Alcohol consumption assessed by the Timeline Follow-back method (TLFB) [21] is the primary study outcome. Using a calendar, respondents provide retrospective estimates of their daily drinking over the previous month. The TLFB has been evaluated with clinical and non-clinical populations [22]The Alcohol Use Disorders Identification Test (AUDIT): a 10-item screening instrument to assess alcohol consumption, drinking behaviors, and harms caused by alcohol use [23]Demographics: age, gender, occupation, marital status (baseline only)General health survey (developed by the GIH) for the assessment of cardiovascular disease and musculoskeletal problems (baseline only). Examples of questions include: have you ever been treated for heart disease? Do you have any injuries that prevent or interfere with exercise?The International Physical Activity Questionnaire (IPAQ) [24]: seven questions assessing the frequency and amount of time spent doing light, moderate, vigorous physical activity, and time spent sitting during the past 7 daysThe Hospital Anxiety Depression Scale (HAD) [25]: 14 items scored 0–3 based on how the respondent felt during the past week. Examples: I feel tense or “wound up”; I get a sudden feelings of panic; I feel as if I am slowed downThe Perceived Stress Scale (PSS) [26]: 10 items scored 0–4 based on how the respondent felt during the past month. Examples: how often have you felt nervous and “stressed”?; how often have you felt that you were on top of things?; how often have you been able to control irritations in your life?The Insomnia Severity Index (ISI) [27]: seven items scored 0–4 based on the respondent’s self-rated sleep quality during the past 2 weeks. Examples: difficulties falling asleep; difficulties staying asleep; problems waking up too earlyThe SF-12 Health Survey [28]: 12 items assess functional health and wellbeing from the respondent’s perspective. The SF-12 covers eight domains: vitality, physical functioning, bodily pain, general health perceptions, physical role functioning, emotional role functioning, social role functioning, and mental healthThe Alcohol Abstinence Self-Efficacy Scale [29]: 12 items scored on a 5-point Likert scale assess how “tempted” or “confident” the respondent feels that they would be to drink in certain situationsThe Cogstate Brief Battery (CBB): a standardized test of cognitive functioning that measures four key domains: psychomotor function, attention, visual learning, and working memory [30, 31]. Participants complete the 12-min test on a laptop computer under supervision

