#### Follow-up assessments and qualitative study

All participants will be contacted by a research assistant at week 6, about half way through the intervention, and invited to attend a short meeting. The purpose will be to (1) hand out the heart-rate monitors with instructions for use and (2) to assess changes in alcohol consumption. Participants who indicate a 50% or more increase in the total volume of alcohol consumed during the past month assessed by the TLFB will be removed from the trial and offered additional clinical support. This assessment will be made by a research assistant with qualifications in nursing or psychology. Participants will be contacted again during week 13 and invited to attend a final follow-up interview. Those who decline will be invited to complete a phone interview or given a shortened baseline questionnaire to return via mail (TLFB, HAD, and physical activity only). Participants will be contacted using a combination of phone calls, emails, and text messaging up to six times over a 2-week period. In addition to collecting quantitative data, we propose to complement these data with a qualitative study. At the post-treatment assessment we propose to conduct semi-structured interviews with participants to determine which aspects of the study, including the exercise intervention, assisted them (or not) and why. During this process, we also propose to assess the acceptability of the interventions among men and women, and younger and older participants. Initial selection will be based on the order of inclusion into the trial. Since we aim for an even distribution across treatment groups, age, and gender, this will also be considered in the selection process. This is a purposive sample; interviews will be analyzed continuously during the data collection period, and the exact number of participants will be determined when “saturation” is reached and no new themes emerge from the interviews. The qualitative part of the study, i.e., developing the interview guide, selecting the participants, data collection, and analyzing the interviews, will be supervised by an experienced qualitative researcher.

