### Statistical analyses and power calculation

Baseline participant characteristics stratified by treatment group will be presented. Group differences will be tested using *t* tests for continuous variables and chi-square tests for categorical outcomes. Parametric test assumptions will be examined and reported. Non-parametric data will be transformed or alternatively analyzed using non-parametric statistical tests. Multiple imputation will be used to replace missing internal values where appropriate. Within-group changes in the primary outcome (alcohol consumption) and secondary outcomes (depression, anxiety, cognitive ability, etc.) will be analyzed using paired-sample *t* tests. To address the primary research question, intention-to-treat analyses will be performed. The effect of group allocation on alcohol consumption and all secondary outcomes at 3-month follow-up will be assessed using mixed linear regression models (logistic for binary outcomes), using both the mean difference (baseline to 3 months) and total scores as dependent variables. Where the total score is used as the outcome, baseline group differences in covariates will be adjusted. As adherence may be sub-optimal, per-protocol analyses will also be presented. Data from individual accelerometers will be pooled to objectively assess changes in physical activity levels before and after treatment. We propose to conduct sub-group analyses based on participant gender and age to assess the effects of these variables on alcohol consumption. All analyses will be performed using SPSS 22.0. All tests will be two-sided and *P* values of less than 0.05 considered statistically significant.

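### The abstract and the Methods disagree on whether AUDIT is a primary outcome, and the mailed week-13 form leaves AUDIT out, so under the abstract's definition part of the primary outcome is missing by design for mail responders

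*Protocol article*

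**What the plan says.** Three places in the protocol article describe the primary outcome.

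- Abstract, Methods: "The primary study outcome is alcohol consumption measure by the Timeline Follow-back method and the Alcohol Use Disorders Identification Test (AUDIT").
- Baseline and follow-up assessments: "Alcohol consumption assessed by the Timeline Follow-back method (TLFB) [21] is the primary study outcome". AUDIT is the next entry in that list. It is described as "a 10-item screening instrument to assess alcohol consumption, drinking behaviors, and harms caused by alcohol use" and is not labelled primary.
- Statistical analyses and power calculation: "Within-group changes in the primary outcome (alcohol consumption"), with no instrument named.

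Follow-up assessments and qualitative study sets out what happens when a participant will not attend at week 13: "Those who decline will be invited to complete a phone interview", or they are "given a shortened baseline questionnaire to return via mail (TLFB, HAD, and physical activity only"). On missing data, the statistics section says: "Multiple imputation will be used to replace missing internal values where appropriate".

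**The concern.** The short form shows which measures the trial wants to keep when contact is limited. It keeps the anxiety and depression scale and physical activity, both secondary according to the abstract. It omits an instrument that the same abstract ranks beside TLFB as primary. Because the list ends with the word for exclusivity, the omission is a fixed choice and not a detail lost in condensing the protocol.

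If AUDIT is primary, the plan builds in a gap for a group defined by its own behaviour: people who declined the visit but returned a form. Such people may plausibly differ in drinking from those who attended. AUDIT items not asked at week 13 cannot be recovered later. If AUDIT is not primary, the abstract is wrong, and readers will expect a primary AUDIT result that the trial did not plan.

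**Working it through.** The point rests on comparing the text. The document gives no figure to reproduce.

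**Step 1: is AUDIT primary?** The abstract says yes. The assessment list gives the primary label to TLFB only. The statistics section does not settle it. Two other details lean towards TLFB alone: the week-6 check on drinking uses TLFB, and the power section counts just two primary comparisons (each exercise arm against TAU), which fits a single primary instrument. Neither detail resolves the conflict.

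**Step 2: what does each week-13 route collect?**

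- Clinic visit: the full assessment, so TLFB and AUDIT.
- Mailed form: TLFB, HAD and physical activity. AUDIT is not collected.
- Phone interview: unclear. The restriction follows the mailed questionnaire in the sentence, and the text does not say whether it also limits the phone call.

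**Step 3: combine the two.**

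- Abstract's definition: mail responders supply one of two primary instruments.
- Methods' definition: mail responders supply the whole primary outcome and lack only a non-primary measure.

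**Step 4: does the missing-data sentence close the gap?** It covers missing internal values. That does not plainly include a whole instrument that was never administered. An analysis plan that is not shown may deal with this, so the imputation sentence is not itself at fault.

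**Step 5: how many people?** The share answering by mail is not given. The expected dropout of about 30% is a different quantity, and the document does not say whether it is counted before or after the fallback. As an illustration only, with 210 randomised and an assumed mail share s, AUDIT is absent by design in 210 × s people:

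- s = 5%: 210 × 0.05 = 10.5, about 10 to 11
- s = 10%: 210 × 0.10 = 21
- s = 20%: 210 × 0.20 = 42

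TLFB would still be requested from all of them.

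**The case against.** The best defence is that the Methods are the operative text and name TLFB alone. On that reading the short form is sensible prioritisation: it protects the primary outcome and sheds a screening instrument. The fallback also removes no AUDIT data that would otherwise exist. Without it, these people would probably supply neither instrument, and the TLFB and HAD it brings in could help to impute AUDIT. All of this stands, and it limits the point. It does not remove the conflict with the abstract, and it does not explain why a secondary scale is kept ahead of an instrument that the abstract calls primary.

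A reader might go further and infer that use of the fallback will differ by arm, because "those randomized to TAU will be offered the 12-week exercise intervention after they have completed the follow-up assessment", and hence that the AUDIT contrast is biased or that the mode of TLFB collection is confounded with arm. The document does not support this. It does not say that a phone or mail return fails to qualify a TAU participant for the offer. The Discussion also describes another incentive, feedback on test scores for those who complete the post-treatment assessment. Whether use of the fallback would differ between arms, and in which direction, is unknown.

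A preference for phone over mail, a table of response mode by arm and a sensitivity analysis without mailed forms are matters of preference or commonly left to the analysis plan. They are not faults here.

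**Conclusion.** The point holds in a limited form. The article contradicts itself on the status of AUDIT, and the mailed form is compatible with only one of its two definitions. Under the abstract's definition, part of the primary outcome is missing by design for every mail responder. Under the Methods' definition, a non-primary measure is missing for the same people.

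Three stronger statements do not follow:

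- The primary outcome is not lost altogether, because TLFB stays on the form.
- The gap is not established for everyone who declines the visit, because the content of the phone interview is unclear.
- No loss of power or size of bias can be given. A bias estimate would need the difference in mail share between arms and the difference in AUDIT between mail responders and attenders. A power estimate would need the number answering by mail. The document states none of these. That mail responders differ is plausible, but it is not documented.

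The consequence is therefore modest and unquantified. It is worth correcting because the correction is cheap and the data cannot be collected afterwards.

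**What to change.** 1. Reconcile the abstract with the section on baseline and follow-up assessments. State once whether AUDIT is primary, co-primary or secondary, and use the same wording in the statistics section.
2. Add the 10 AUDIT items to the shortened mailed questionnaire. State what the phone interview contains and, if it is shortened in the same way, add AUDIT there too.

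The second change is needed if AUDIT is primary or co-primary. If it is secondary, the change is still a cheap gain, because it avoids a gap that the form itself would leave. It should be made before week-13 follow-up begins. The cost is about one page on the mailed form; the downside is a slightly longer form, with a small possible loss of returns.

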### Statistical analyses and power calculation

Baseline participant characteristics stratified by treatment group will be presented. Group differences will be tested using *t* tests for continuous variables and chi-square tests for categorical outcomes. Parametric test assumptions will be examined and reported. Non-parametric data will be transformed or alternatively analyzed using non-parametric statistical tests. Multiple imputation will be used to replace missing internal values where appropriate. Within-group changes in the primary outcome (alcohol consumption) and secondary outcomes (depression, anxiety, cognitive ability, etc.) will be analyzed using paired-sample *t* tests. To address the primary research question, intention-to-treat analyses will be performed. The effect of group allocation on alcohol consumption and all secondary outcomes at 3-month follow-up will be assessed using mixed linear regression models (logistic for binary outcomes), using both the mean difference (baseline to 3 months) and total scores as dependent variables. Where the total score is used as the outcome, baseline group differences in covariates will be adjusted. As adherence may be sub-optimal, per-protocol analyses will also be presented. Data from individual accelerometers will be pooled to objectively assess changes in physical activity levels before and after treatment. We propose to conduct sub-group analyses based on participant gender and age to assess the effects of these variables on alcohol consumption. All analyses will be performed using SPSS 22.0. All tests will be two-sided and *P* values of less than 0.05 considered statistically significant.

Our sample size calculation is based on a preliminary study of the effects of exercise on alcohol consumption by Brown et al., 2015 [38]. Using this study as a guide, we anticipate a standardized mean difference (effect size) of around 0.3 favoring the yoga and aerobic exercise groups equally, compared to TAU. Our recent meta-analysis identified a pooled dropout rate of 40% from exercise for AUD studies. Due to the incentives in our trial, we estimate a slightly lower dropout of around 30%. Based on these parameters, with an 80% power, two-tailed significance of 2.5% to allow for two primary between-group comparisons (yoga versus TAU, and aerobic exercise versus TAU), and 1:1:1 allocation, we estimate that a total sample size of 210 participants will be required (i.e., 70 in each group). We used the program G*Power to determine sample sizes [39].

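### Alcohol consumption is analysed as both change and total score with neither named primary, and adjustment for baseline consumption is not guaranteed

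*Protocol article*

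**What the plan says.** All the relevant text is in the protocol article, section Statistical analyses and power calculation.

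- **Two dependent variables.** The between-group models for drinking, and for every secondary measure, are mixed linear models, or logistic where the measure is binary. They are to be fitted "using both the mean difference (baseline to 3 months) and total scores as dependent variables". Neither score is called primary, and nothing says what happens if they disagree.
- **Covariates.** "Where the total score is used as the outcome, baseline group differences in covariates will be adjusted". No covariate is named, baseline consumption is not mentioned, and no adjustment is stated for the change-score model.
- **Baseline tests.** Directly after announcing the baseline table by group, the section says "Group differences will be tested using" t tests or chi-square tests.
- **Significance level.** The sample size paragraph uses a "two-tailed significance of 2.5% to allow for two primary between-group comparisons", namely yoga against TAU and aerobic exercise against TAU. The analysis paragraph declares *P* "values of less than 0.05 considered statistically significant" for all tests, with no exception for the primary comparisons.

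**The concern.** There are two separate weaknesses, with different consequences.

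**Two versions of one outcome.** Change and total score are different tests of the same hypothesis and can disagree. With no ranking, the more favourable can be presented as the answer to the primary question once the data are seen. The 2.5% level is fully spent on the two arm comparisons, so nothing is left to pay for a second score.

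**Baseline adjustment left to circumstance.** The most natural reading of the covariate sentence, coming after the announced baseline tests, is that covariates enter where the groups are seen to differ. Baseline drinking is likely to predict follow-up drinking. A model that includes it only on observed imbalance usually gives up the precision that it offers. The change score does use baseline, but with a fixed coefficient of 1, which is inefficient unless the pre/post correlation is high.

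**Working it through.** **Inputs from the article:** 70 per arm; 30% dropout, so 0.7 × 70 = 49 completers per arm; standardised mean difference 0.3; two comparisons with TAU at two-sided 2.5%; general level 0.05.

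**Assumptions:** a pre/post correlation r, which the article does not give, set to 0.3, 0.5 and 0.7; normal data with equal SD at both times; and, for the error rates, that significance on either score counts as success.

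**The plan's own allowance.** Two comparisons at 5% / 2 = 2.5% each. If independent, the family-wise error is 1 − 0.975² = 4.9%. Because both share the TAU arm, simulation gives about 4.7%. The allowance therefore works for one score. (The stated 80% power does not follow from these inputs: unadjusted, 49 per arm gives about 22%. That is a separate sample size matter.)

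**Error from two scores, one comparison.** The change-score and unadjusted total-score estimates have correlation √((1 − r)/2) = 0.59 / 0.50 / 0.39 at r = 0.3 / 0.5 / 0.7. With the total score always adjusted for baseline, the correlation is √((1 + r)/2) = 0.81 / 0.87 / 0.92. The chance under the null that at least one of the two tests passes 0.025 is then:

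- unadjusted total or change: 4.5% / 4.6% / 4.7%
- baseline-adjusted total or change: 4.0% / 3.8% / 3.5%

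**Error from two scores, both comparisons.** Three arms of 49 were simulated with no effect, over r = 0.3 to 0.7. Imbalance-triggered adjustment was modelled as adjustment when the baseline test gives P < 0.05.

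| Tested in each comparison | Family-wise error at 0.025 per test |
|---|---|
| One score | about 4.7% |
| Change, or total always adjusted for baseline | 6.4-7.5% |
| Change, or total adjusted only on imbalance | 7.1-8.1% |
| Change, or unadjusted total | 8.5-8.7% |

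At 0.05 per test the three two-score versions span about 12-17%, against about 9% for one score.

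**Error from the covariate rule alone.** Total score only, adjusted on imbalance: about 1.6-2.5% per comparison for a nominal 2.5%. The rule is conservative.

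**Power.** By the normal approximation, power = Φ(0.3 / (k√(2/49)) − 2.241), where k = 1 for the unadjusted total, √(2(1 − r)) for change and √(1 − r²) for the total always adjusted for baseline. Since √(2/49) = 0.202, the unadjusted case is Φ(1.485 − 2.241) = 22.5%. At r = 0.7 the adjusted case has k = 0.714, giving Φ(2.079 − 2.241) = 43.6%. Simulation with t tests gives slightly lower values:

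| Analysis | r = 0.3 | r = 0.5 | r = 0.7 |
|---|---|---|---|
| Total, adjusted only on imbalance | about 22% | about 22% | about 22% |
| Change score | 16% | 22% | 36% |
| Total, always adjusted for baseline | 24% | 29% | 42% |

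Always adjusting does best at each correlation. The gain over the imbalance rule is small at r = 0.3 (about 2 points) and large at r = 0.7 (about 20 points).

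**The case against.** The strongest reply is that a journal article condenses the plan, and that ranking the scores and listing covariates belong in a statistical analysis plan not shown here. This stands for the covariate list as such, and for the choice of transformation or rank test when assumptions fail. Those are routine detail and no part of this point. Nor is the mention of t tests with three groups, since t tests can be pairwise. The reply does not cover the two dependent variables: the article states them affirmatively for the primary question, so a later plan would have to overrule the sentence, not fill a gap.

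A second reply is that the covariate sentence sets no significance threshold and does not refer back to the baseline tests; it could mean that baseline differences are adjusted for as a rule. That is fair. A reader might infer a P < 0.05 trigger, but the text does not state one. What can be said is that adjustment for baseline consumption is not guaranteed. Even on the generous reading, with the total score always adjusted, testing both scores still gives 6.4-7.5%.

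Third, the article never says that success on either score would be claimed. Also true: the error figures are conditional on that.

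**Conclusion.** The point holds in two parts, which should be kept apart.

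1. Two unranked scores for the primary outcome raise family-wise error to about 6.4-8.7% at 0.025 per test, against about 4.7% with one score, if either may count as success.
2. Baseline adjustment is not assured. On the natural reading this costs between about 2 and 20 percentage points of power, according to the correlation.

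Two stronger readings are tempting and not supported. One is that adjusting on observed imbalance itself inflates type I error; it is conservative, and its harm is lost power. The other is to set the 12-17% at level 0.05 against 4.7%; that comparator belongs to level 0.025. At 0.05 a single score already gives about 9%, and that part of the rise comes from the separate conflict between the 2.5% and 0.05 levels.

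The direction of the power result is the same at all three assumed correlations; its size depends on a correlation that the article does not give. Even the best case, 42%, leaves the trial well short of 80%, so this change improves precision but does not cure the sample size. It should be made; it is not a fatal flaw.

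**What to change.** Name one primary between-group analysis: week-13 TLFB consumption, on a scale fixed in advance, within the planned regression framework and always adjusted for baseline TLFB consumption. Test it at 2.5% for each of the two comparisons with TAU, and make the general 0.05 statement except these two tests. TLFB is used here because the section on baseline and follow-up assessments names it as the primary outcome.

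Designate the change-score model as supportive. Present baseline characteristics descriptively, and state that observed baseline differences will not decide the covariates. Adding sex and age as fixed covariates is optional.

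Cost: analysis wording only. TLFB is already collected at baseline and at week 13.

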### Key research questions

What are the effects of yoga and aerobic exercise on alcohol consumption in AUD patients?Does regular exercise reduce depression and anxiety, and improve self-efficacy in those with an AUD?Does exercise reduce stress and improve sleep quality in AUDs?Can exercise improve cognitive functioning in AUD patients?Does regular exercise improve health-related quality of life in AUD patients?What are the effects of exercise on cardiovascular risk factors and sedentary behavior?What are the effects of acute exercise on the urge to drink alcohol, mood, and anxiety? (nested study)What are participants’ subjective experiences of the intervention? (qualitative study)

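### One P<0.05 rule covers every test, so the secondary outcomes behind the yes/no key questions can be declared significant with no multiplicity allowance and no exploratory label

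*Protocol article*

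**What the plan says.** All references are to the Protocol article.

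- **Key research questions.** Questions 2 to 5 are put in yes/no form, for example "Does regular exercise reduce depression and anxiety, and improve self-efficacy in those with an AUD". The others in this group concern stress and sleep, cognition, and quality of life. Question 6, on cardiovascular risk factors and sedentary behaviour, is open-ended.
- **Abstract, Methods.** These outcomes are ranked below alcohol consumption: "Secondary outcomes include: depression, anxiety, perceived stress, sleep quality, physical activity levels, fitness, self-efficacy, health-related quality of life, and cognition".
- **Baseline and follow-up assessments.** Some questions rest on several scores. The cognitive battery is "a standardized test of cognitive functioning that measures four key domains: psychomotor function, attention, visual learning, and working memory", and the SF-12 is described as covering eight domains.
- **Statistical analyses and power calculation, analysis paragraph.** "The effect of group allocation on alcohol consumption and all secondary outcomes at 3-month follow-up will be assessed using mixed linear regression models", with both the change from baseline and the total score as dependent variables. Within-group paired t tests and per-protocol analyses are added. The closing rule is "All tests will be two-sided and *P* values of less than 0.05 considered statistically significant".
- **Same section, sample-size paragraph.** The calculation uses a "two-tailed significance of 2.5% to allow for two primary between-group comparisons (yoga versus TAU, and aerobic exercise versus TAU".

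**The concern.** This is a decision rule that the document states, not a detail left open. The rule gives every secondary test the full 5%, although the sponsor saw the need for an allowance on the primary outcome. Nothing in the document orders the secondary outcomes among themselves, adjusts for their number or calls them exploratory. Nor does it say which score or which arm would answer a question such as whether exercise improves cognition.

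At stake is how the results may be described. With many scores and two exercise arms, a few results below 0.05 are expected by chance, and the rule lets each be reported as a significant answer to a key question.

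The sentence also makes no exception for the primary outcome. Read literally, it judges the two primary contrasts at 5%, while the sample-size paragraph plans 2.5% for each.

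**Working it through.** **The plan's own figure.** The document gives no family-wise error rate for the secondary outcomes. Its only multiplicity figure is the primary level: 0.05 / 2 = 0.025. This reproduces exactly, but it covers two tests on one outcome.

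**Inputs from the document.** Two-sided 0.05 per test, so 0.025 in the direction favouring exercise; three equal arms; two dependent variables per outcome.

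**Count of scores.** The abstract's list gives depression, anxiety, stress, sleep, physical activity, fitness, self-efficacy and quality of life (8, one score each) plus four cognitive domains, so 8 + 4 = 12. Questions 2 to 5 alone give 2 (depression, anxiety) + 1 (self-efficacy) + 2 (stress, sleep) + 4 (cognition) + 2 (SF-12, if two summary scores are assumed) = 11, or 17 with eight SF-12 domains. Twelve is a reasonable working number.

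**Assumptions.**
1. Each score is compared with TAU in both exercise arms, so 12 × 2 = 24 tests.
2. No score has a true effect.
3. Scores share a common correlation r, shown from 0 to 0.8.
4. Where both dependent variables are counted, the correlation of baseline with follow-up is 0.6.

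**Independence benchmark.** Expected false positives: 24 × 0.05 = 1.2, of which 24 × 0.025 = 0.6 favour exercise. P(any) = 1 − 0.95^24 = 70.8%. P(any favouring exercise) = 1 − 0.975^24 = 45.5%.

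**Simulation.** For each arm, draw 12 equicorrelated standard normal scores. For each score, form z = (exercise arm − TAU) / √2 for yoga and for aerobic training. The two contrasts share TAU, so they correlate 0.5. Count a false result when |z| > 1.96 (either direction) or z > 1.96 (favouring exercise). For the last column, follow-up = 0.6 × baseline + 0.8 × independent noise, and a score counts if either the change or the unadjusted total passes 1.96.

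| r | Any P<0.05, one analysis | Favouring exercise, one analysis | Favouring exercise, change and total |
|---|---|---|---|
| 0 | 68% | 43% | 64% |
| 0.3 | 61% | 33% | 51% |
| 0.5 | 51% | 26% | 42% |
| 0.8 | 31% | 16% | 26% |

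**Sensitivity.**
- If the total-score model adjusts for the outcome's own baseline, the last column falls to about 55, 42, 34 and 21%.
- Fitness and depression are the two outcomes on which the Discussion expects benefit. Dropping them leaves 10 scores, and the single-analysis figure favouring exercise is about 37, 29 and 24% at r = 0, 0.3 and 0.5.
- For the cognition question alone (4 domains × 2 arms), a false favourable result has a chance of about 13% at r = 0.5 and 10% at r = 0.8.

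**The case against.** The case against has several sound parts.

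- **Direction.** A reader might infer that a false claim of benefit is about as likely as not. The 51% at r = 0.5 counts results in either direction, including those showing exercise to be worse. With one analysis per score, the favourable figure at that correlation is 26%. It reaches about one half only with weakly correlated scores and both dependent variables counted.
- **Number of tests.** The two exercise-versus-TAU contrasts are named only for the primary outcome. For secondary outcomes the text speaks only of group allocation, which would also fit an overall group test. Twenty-four tests is an inference.
- **Global null.** The Discussion expects positive effects on physical fitness and depression, so no effect on any score is a worst case.
- **Ranking.** It would be wrong to say that there is no hierarchy. The outcomes are labelled secondary to alcohol consumption, and unadjusted secondary tests are common practice.
- **Question form.** Not all the key questions are yes/no. Those on alcohol consumption and on cardiovascular risk are open-ended.
- **Scope.** An analysis plan not shown may order or label the secondary outcomes.

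The last objection would decide the matter if the article were silent, but it states a threshold for all tests. A label of secondary gives rank but does not limit what that threshold lets the report call significant. The other objections reduce the size and grade of the point without removing it.

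**Conclusion.** The point holds as a minor one. The stated rule lets any secondary result below 0.05 be called significant, on outcomes posed as yes/no key questions, with no allowance for their number. Under the worst-case null and the inferred two contrasts per score, the chance of at least one false result favouring exercise is about 16 to 43% with one analysis per score. It is about 26 to 64% with both dependent variables, the total taken as unadjusted for its own baseline. For a false result in either direction, one analysis per score gives about 31 to 68%. The ranges reflect the assumed between-score correlation, which the document does not give. The two-variable range also rests on the assumed baseline correlation of 0.6.

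The document does not support a single headline such as one half. Nor does it show that the sponsor intends to rely on secondary results if the primary outcome is null. Separately, and without any assumption, the 0.05 sentence disagrees with the 2.5% planned for the two primary contrasts.

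**What to change.** In the analysis paragraph of Statistical analyses and power calculation, limit the P<0.05 sentence so that it no longer defines significance for secondary outcomes. State that the secondary outcomes are exploratory and will be reported as estimates with confidence intervals, without claims of significance. In the same edit, state the level at which each of the two primary contrasts will be judged, so that the sentence agrees with the 2.5% in the sample-size paragraph.

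A formal procedure is possible: one named measure and contrast per question, tested by Holm after the primary succeeds. That is a design preference and is not needed to cure the fault.

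The change is wording only and affects neither data collection nor sample size. Its cost is that fewer secondary results can be called significant.
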